## Background

Men who have sex with men (MSM) have been identified as one of the key populations in the HIV epidemic. The prevalence of HIV among MSM in China has been rapidly and continuously increasing, especially in metropolitan cities such as Beijing, Guangzhou, and Chengdu [1–3]. The pooled prevalence of HIV infection among MSM soared from 1.4% in 2001 to 9.0% in 2013 [4], and transmissions between MSM accounted for 25.5% of the new HIV infections in 2017 [5].

‘Treatment as Prevention’ (TasP) is a promising strategy for HIV prevention and control. In 2016, the Chinese Centre for Disease Control and Prevention (CDC) revised the national guidelines for antiretroviral treatment (ART) and suggested immediate treatment for all people living with HIV/AIDS (PLWHA) [6]. However, the long-term success of such efforts to scale-up coverage of ART for PLWHA may be negatively affected by deficits in adherence to the spectrum of HIV care. ART requires adequate adherence (usually defined as intake of at least 95% of ART doses [7, 8]) to yield satisfactory clinical outcomes, e.g., suppressing HIV viral replication [9], improving quality of life [10], and preventing transmission [11]. However, a recent meta-analysis indicated that only 77.6% (95% confidence interval [CI]: 71.6–83.1) of Chinese PLWHA on ART maintained adequate adherence [12]. Barriers to ART adherence include patient factors (e.g., education, lack of self-efficacy, mental illness), medication factors (e.g., side effects, pill burden, and food requirement), and system of care (e.g., linkage of care, negative experiences of healthcare system) [13–15]. Moreover, MSM can experience a fear of disclosure in public and healthcare settings and the stigma associated with their sexual orientation [16]. Thus, the ART adherence of this group warrants more attention.

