### Participants

#### Eligibility criteria

The participant inclusion criteria are as follows: 1) male, aged ≥18; 2) HIV-positive; 3) ART-naïve, and planning to initiate ART on the day of recruitment; 4) self-reported to be HIV-infected through homosexual transmission; 5) having access to the Internet on a smartphone; 6) having a WeChat account and using it in daily communication; 7) willing to provide written informed consent. Participants who have been hospitalized due to severe opportunistic infections are excluded.

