#### Secondary outcomes

***HIV-1 RNA*** viral load at month 12 was measured by polymerase chain reaction (PCR).

***Mental health*** status includes anxiety and depression, which are measured by the seven-item Generalized Anxiety Disorder-7 (GAD-7) instrument [48] and nine-item Patient Health Questionnaire-9 (PHQ-9) [49], respectively. Both instruments comprise four-point Likert scales with the responses based on occurrence of symptoms during the last week. In each scale, the sum of all items will be calculated and categorized into different levels of mental health disorder: normal (0–4), mild (5–9), moderate (10–14), and moderate to severe (≥15) [50, 51].

***Quality of life*** is measured by the 31-item HIV adaptation of the World Health Organization Quality of Life scale (WHOQOL-HIV bref) [52], which has shown good reliability and validity among Chinese PLWHA [53]. The scale consists of six domains: physical health, level of independence, psychological health, spirituality, social relations and environmental health. For each domain, a score ranging from 4 to 20 will be calculated, with higher scores denoting better quality of life.

***Illness representation*** is measured by the Brief Illness Perception Questionnaire (B-IPQ), which has been used among PLWHA to evaluate their cognitive and emotional response towards HIV [54]. The B-IPQ comprises the following eight dimensions: consequences, timeline, personal control, treatment control, identity, coherence, concern, and emotional response. Each dimension has only one question, with responses rated on a scale from 0 to 10. A higher score indicates a greater perception of a threat from HIV [55].

***ART-related perception*** is measured by the Life Windows Information-Motivation- Behavioural Skills ART Adherence Questionnaire (LW-IMB-AAD) [56]. The instrument consists of 33 items rated on a 5-point Likert scale, with nine measuring information, ten measuring motivation, and 14 measuring behavioural skills. Summative scores are computed for each aspect, with higher scores reflecting better information, motivation and behavioural skills about adherence [57].

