### Sample size estimation

We will calculate the size of effect that the sample size in our study can detect with 80% power (two-tailed alpha 0.05) with regard to the primary outcome. Based on previous studies conducted among Chinese MSM that newly initiate ART, we estimate that the adherent rate at month six in the control group will be 89% [14]. The target sample size of 600 (300 in each arm) will be powered to detect a smallest between-group difference of 9% in adherent rates, allowing for a 20% attrition rate at month six.

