#### Effectiveness of intervention

The primary outcomes will be the prevalence of ART adherence and CD4 counts at month six. For the between-group comparisons, *χ*^*2*^ test will be used for binary outcomes (e.g., ART adherence, mental health disorders, sexual risk behaviours) and *t*-test for continuous outcomes (e.g., CD4 count, quality of life, illness representation, IMB constructs, and HIV viral load). Within-subject analyses will also be conducted, comparing the baseline response to follow-up session responses.

Intervention effects will be performed on the principle of intention-to-treat (ITT), using the data collected from all randomized participants in the analysis. Missing endpoints will be imputed by Multiple-Imputation approach. The General estimating equation (GEE) will be used for repeated measures analyses using SAS 9.0, which allows for the inclusion of all subjects in the analysis regardless of their number of visits. As GEEs require data to be randomly missing, the analysis will be repeated using a subset of participants with complete data. A sensitivity analysis will be conducted to determine the impact of dropout and to evaluate additional longer timeframes (month 12).

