There are a few study limitations worth noting. Most importantly, the open study-design means that we cannot mask the intervention, thus participants will be aware that they are part of an ART adherence intervention, which might introduce bias. Although self-reported adherence to ART has notable defects, we have adopted a composite and sensitive measurement scale, using CD4 counts and HIV-RNA levels as objective indicators of efficacy. In addition, we will not be able to control external factors that may confound study results, although we will document some potential confounders (e.g., health information received from other sources or other health programmes occurring in the intervention period) to help with the interpretation of findings.

This trial is among the first efforts to innovatively develop and test the smartphone APP-based case management mHealth intervention in China. Once proven effective, the innovative mHealth service could be integrated into the routine case management of PLWH. This mHealth intervention could also tailored to the patient management service for other chronic conditions. The trial is currently ongoing and the intervention effects will be reported after the data collection.

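### Month-12 HIV viral load is assigned to a t-test, which loses power when most values lie at the assay limit; the proportion suppressed is the better comparison

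*Protocol article*

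**What the plan says.** In the Protocol article, Statistical analysis, Effectiveness of intervention, binary outcomes go to a chi-square test. The other outcomes go to a t-"test for continuous outcomes (e.g., CD4 count, quality of life, illness representation, IMB constructs, and HIV viral load". The list of t-test examples thus closes with "IMB constructs, and HIV viral load". Adherence, mental health disorders and sexual risk behaviours are the examples given for the chi-square test; viral load is not among them.

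The Secondary outcomes section places the measurement in time: "viral load at month 12 was measured by polymerase chain reaction (PCR". It gives no unit or scale, no rule for results below the detection limit and no suppression threshold.

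Three other statements bear on what the data will look like:
- Eligibility criteria: participants are "ART-naïve, and planning to initiate ART on the day of recruitment", so month 12 is about one year on treatment.
- Background: adequate adherence is linked to "suppressing HIV viral replication".
- Sample size estimation: "we estimate that the adherent rate at month six in the control group will be 89" per cent.

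The limitations part of the Discussion answers the weakness of self-reported adherence in an open-label trial by "using CD4 counts and HIV-RNA levels as objective indicators of efficacy".

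**The concern.** A t-test compares arm means. It suits an outcome whose mean summarises a typical patient and whose variance is not set by a few observations. Viral load after a year of first-line treatment is unlikely to be such an outcome. Suppressed patients return a result below the detection limit, which is not a number and must be given one before it can be averaged. The remaining patients can differ from each other by several orders of magnitude. On the copies/mL scale, the mean and variance of an arm of 240 are then set mostly by its highest few values.

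At stake is whether the trial can see a difference in suppression if there is one. Viral load is secondary, but the article relies on it as one of two laboratory measures to set beside a self-reported, unmasked primary outcome. A null result from a test with little power would be hard to interpret in that role.

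**Working it through.** **The plan's own figure.** The article states no power, suppression rate or effect size for viral load, so there is nothing to reproduce. Its sample size concerns adherence only ("smallest between-group difference of 9% in adherent rates").

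**Inputs from the article.** There are 300 per arm, 20% attrition at month 6 and a two-sided alpha of 0.05. Evaluable patients: 300 × (1 − 0.20) = 240 per arm.

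**Assumptions, not in the article.**
- The month-6 attrition also applies at month 12.
- Suppressed results are set to 50 copies/mL.
- Viraemic values are either log-uniform from 10^2 to 10^6, or log-normal with log10 mean 4 and SD 1. The distribution is the same in both arms.
- Suppression is 90% v 96%, or 85% v 93%.

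**Approximate power by hand: log-uniform viraemia, viraemic 10% v 4%.** For an arm with viraemic proportion p, let m and M be the first and second moments of the viraemic values (measured from the limit for log10). The arm mean is pm and the variance is pM − (pm)². Power ≈ Φ(difference/SE − 1.96).

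*Raw copies.*
- m ≈ (10^6 − 10^2)/ln(10^4) = 999,900/9.2103 ≈ 108,563. M ≈ 10^12/(2 × 9.2103) ≈ 5.429 × 10^10. The 50-copy floor is negligible here.
- Difference: 0.06 × (108,563 − 50) ≈ 6,511.
- Variances ≈ 5.311 × 10^9 and 2.153 × 10^9. SE = √(7.463 × 10^9/240) ≈ 5,577.
- Ratio 1.17; power ≈ Φ(−0.79) ≈ 21%.

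*Log10 copies.*
- log10 50 = 1.699, so m = 4 − 1.699 = 2.301. M = 16/12 + 2.301² = 6.628.
- Difference: 0.06 × 2.301 = 0.138.
- Variances: 0.610 and 0.257. SE = √(0.867/240) ≈ 0.0601.
- Ratio 2.30; power ≈ Φ(0.34) ≈ 63%.

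*Suppressed yes/no.*
- Pooled SE = √(2 × 0.07 × 0.93/240) ≈ 0.0233. Unpooled SE = √((0.09 + 0.0384)/240) ≈ 0.0231.
- Power ≈ Φ((0.06 − 1.96 × 0.0233)/0.0231) ≈ Φ(0.62) ≈ 73%.

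**Simulation, 6,000 trials per row, 240 per arm.** The last column is the median share of the total sum of squares of raw copies carried by the 5 most extreme of 480 patients.

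| Suppressed | Viraemic values | Raw t | Log10 t | Chi-square | Top-5 share |
|---|---|---|---|---|---|
| 90% v 96% | log-uniform | 23% | 65% | 74% | 91% |
| 90% v 96% | log-normal | 10% | 67% | 74% | 98% |
| 85% v 93% | log-uniform | 25% | 71% | 81% | 80% |
| 85% v 93% | log-normal | 11% | 74% | 81% | 97% |

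Repeat runs with other seeds differ by a point or two, which gives the ranges quoted in the summary.

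**Type I error.** With 5%, 10% or 15% viraemic in both arms, the raw t-test rejects about 1–2% of the time under log-normal viraemia and about 3–5% under log-uniform, against a nominal 5%. The log10 t-test and the chi-square test stay close to 5%.

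**Can one or two patients produce significance?** Put k patients at 10^6 copies in one arm and everyone else at 50. Then t ≈ √k: k = 1 gives p = 0.32, k = 2 gives 0.16, k = 3 gives 0.08 and k = 4 gives 0.045.

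**The case against.** The strongest reply is that the article never says copies/mL. Measurement scale and the handling of results below the limit are details that a condensed article can leave to a full protocol or SAP, and neither is shown. If the analysts use log10, the t-test keeps its size and most of its power. This stands, and it narrows the point: the very low power figures apply only to raw values. The named test remains the weaker choice, because on log10 it was still about 7–10 points behind the chi-square test. It also needs a number for results below the limit, although that effect is modest: using 20 instead of 50 copies in the hand calculation gives m = 2.699, ratio 2.37 and power of about 66% rather than 63%.

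A reader might infer that one or two patients with rebound could create a significant result. The check above does not support this: four at 10^6 copies, all in one arm, are needed, and the raw test does not exceed its nominal level.

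A reader might also infer that the 89% is a suppression rate, or that the plan rules out an analysis of suppression. Neither is stated. The 89% is self-reported adherence in the control arm at month 6, and both lists of outcomes are introduced as examples.

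Finally, viral load is secondary and is measured six months after the intervention ends, so it is not a same-time check on month-6 adherence; CD4 count, a co-primary outcome, fills that role. This limits the severity.

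**Conclusion.** The point holds at moderate severity. The article names a t-test for an outcome that will plausibly be a large mass at the assay limit plus a few widely spread values. Against a chi-square test on suppression, the loss in the scenarios above is roughly 50 to 70 percentage points of power on raw copies and about 7–10 points on log10 copies. On the raw scale, five patients typically carry 80–98% of the variability.

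The size rests on assumed suppression rates, detection limit, viraemic distribution and month-12 attrition. It also assumes that the intervention changes how many patients are viraemic rather than how high their values are. The ordering of the three tests was the same in every scenario tried, including others with 2–20% viraemic. The evidence is of lost power and a poorly representative mean. It does not show spurious findings, and it does not touch the primary analysis.

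**What to change.** In Effectiveness of intervention, remove HIV viral load from the t-test examples. State the viral-load endpoint as the proportion of participants with HIV RNA below the assay's detection limit at month 12, and give that limit. Compare the arms by chi-square test or logistic regression, reporting the risk difference with its 95% confidence interval. As support, and to keep information on the level of viraemia, add a rank-based comparison or a censored (Tobit) model on log10 values, with results below the limit treated as censored. Make the matching change under Secondary outcomes.

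The cost is analysis wording only: samples, assay, visit schedule and sample size are unchanged. The change should be dated before month-12 viral loads are compared by arm.

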**Methods:**

A non-blinded 1:1 parallel-group randomised controlled trial will be conducted in Guangzhou Eighth People’s Hospital, with 300 MSM enrolled in each arm. Eligible MSM who are newly initiating ART will be randomly assigned to an intervention group (standard-of-care case management plus mHealth intervention) or a control group (standard-of-care case management). The development of the mHealth intervention will be based on the information–motivation–behavioural skills theory of ART adherence, and comprise four components: educational articles, one-to-one online communication with case managers, support-service information and hospital-visit reminders. Outcome measures will be collected at baseline and at months 1, 3, 6, and 12. The primary outcomes will be ART adherence and CD4 count at month 6. Secondary outcomes include HIV RNA, sexual behaviours, mental health status, illness perceptions, and quality of life. *χ*^*2*^ test and t-test will be used for between-group comparisons. Intervention effects will be evaluated using General estimating equation performed by SAS 9.0, on the principle of intention-to-treat. Structural equation modelling will be used to test potential mechanisms of intervention effect.

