### Measures

#### Primary outcome

The primary outcome of this study is self-reported ART medication adherence and CD4 count at month six. As literature studies have shown that self-reported adherence is usually positively skewed, mostly due to social desirability bias and recall bias [45], we adopt a composite scale that has high sensitivity [46]. This scale consists of three adherence items measuring medication-taking adherence in the preceding 30 days: 1) a ‘days missed’ item, in which participants are asked the number of days they have missed an ART dose; 2) a ‘rating’ item, in which participants are asked to rate their pill-taking performance; 3) a ‘frequency’ item, in which participants are asked how frequently they took their pills according to instructions. Cronbach’s alpha was 0.86 in the previously reported study using this scale [47]. Moreover, item responses for the three adherence items were linearly transformed to a 0–100 scale and the average scores of all three items are used. A summary of the individual adherence items was calculated as the mean of the three individual items. In this study, we consider anyone scoring below the maximum score on any item as non-adherent (i.e., a combined scale score of < 100). CD4 counts are examined in each physical test and measured by flow cytometer. The months one and three assessments allow for trend evaluation and the month 12 assessments will allow for evaluation of persistent effect of intervention, but these are not the primary outcomes.

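### Two between-arm analyses are stated for the month-6 primary outcomes (chi-square/t-test and a repeated-measures GEE), and the plan does not say which one decides the trial

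*Protocol article*

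**What the plan says.** In the protocol article, *Effectiveness of intervention* sets the endpoint: "The primary outcomes will be the prevalence of ART adherence and CD4 counts at month six". *Primary outcome* says of the assessments at months 1, 3 and 12, which serve trend and persistence, "but these are not the primary outcomes".

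For between-group comparisons the chi-square "test will be used for binary outcomes (e.g., ART adherence, mental health disorders, sexual risk behaviours)", and the t-test is for "continuous outcomes (e.g., CD4 count, quality of life, illness representation, IMB constructs, and HIV viral load)". Each primary outcome is therefore named under a single-visit test.

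The next paragraph, which opens with intervention effects under intention-to-treat, adds: "The General estimating equation (GEE) will be used for repeated measures analyses using SAS 9.0". The *Methods* paragraph of the abstract lists chi-square and t-test for between-group comparisons and continues: "Intervention effects will be evaluated using General estimating equation performed by SAS 9.0, on the principle of intention-to-treat".

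Two smaller statements bear on the point. One is "Within-subject analyses will also be conducted, comparing the baseline response to follow-up session responses". The other places the month-12 timeframe under a sensitivity analysis.

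**The concern.** In a two-arm trial the between-group comparison is the intervention effect. The abstract separates the two and gives them different methods, and the main text does not settle which governs. That is more than a missing modelling detail: the article makes two statements about how the primary outcomes are judged, and they point to different analyses.

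The two need not estimate the same thing. The single-visit test addresses month 6. A repeated-measures GEE addresses month 6 only if it contains a visit-specific contrast; with a single arm effect it would average over visits that the article says are not primary. If the results differ, a reader has no stated basis for knowing which one counts.

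**Working it through.** **The plan's own figures.** The article gives no figure on this point. Its *Sample size estimation* section supplies the setting: 300 per arm, 20% attrition, two-sided 0.05, control adherence 89% at month 6. That leaves 300 × 0.8 = 240 per arm. The stated 9-point detectable difference does not reproduce for an improvement (89% against 98% with 240 per arm has 98.1% power, not 80%). That is a separate matter and nothing below depends on it.

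**Step 1: how closely the two tests are related.** Assume equal variances and exchangeable correlation r between visits. The correlation between a month-6 mean and a k-visit average is √[(1 + (k − 1)r)/k].

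- k = 3: 0.73 at r = 0.3; 0.89 at r = 0.7
- k = 4: 0.69 at r = 0.3; 0.88 at r = 0.7

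A range of 0.7 to 0.9 is therefore a fair assumption.

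**Step 2: type I error if either test may count.** For bivariate normal statistics with correlation ρ, the error is 1 − P(|Z₁| ≤ 1.96 and |Z₂| ≤ 1.96).

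| ρ | Error |
|---|---|
| 0.7 | 8.3% |
| 0.8 | 7.8% |
| 0.9 | 7.0% |

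A simulation agrees. It used 20,000 trials per scenario, 240 per arm, adherence 89% in both arms, and a latent-normal correlation of 0.3, 0.5 or 0.7. The month-6 two-proportion test was compared with an arm effect averaged over months 1, 3 and 6 (independence working correlation, identity link, robust standard error). Each test alone rejects in about 5%, at least one of them in 7.8% to 8.7%, and they disagree in 5.9% to 7.3% of trials.

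**Step 3: direction of the difference when there is an effect.** Control is 89% throughout. The intervention rates at months 1, 3 and 6 are assumed.

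| Profile | Rates | Month-6 difference | Average difference | Power, month-6 test | Power, averaged | Disagree |
|---|---|---|---|---|---|---|
| Fading | 96/95/93% | 4 points | (7+6+4)/3 = 5.7 | 33–34% | 85–95% | 52–62% |
| Late | 89/92/96% | 7 points | (0+3+7)/3 = 3.3 | 85% | 38–50% | 39–47% |

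The averaged effect can lie on either side of the month-6 effect. Neither direction can be presumed: article delivery thins from daily to weekly, which could produce fading, while skills or CD4 gains could accumulate.

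**The case against.** The strongest reply is that the main text can be read coherently. It sets month 6 as primary, then names adherence and CD4 under the chi-square and t-test, and gives the GEE a separate job on repeated measures. The other visits are for trend and persistence, and the sample size rests on month-6 adherence rates, which fits a two-proportion test. Visit coding and contrasts for a GEE commonly sit in an analysis plan, and with an arm-by-visit term and a month-6 contrast the GEE would largely agree with the single-visit test.

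Much of this stands. The absence of GEE modelling detail is not a finding in itself. What remains is that the abstract attaches the intervention effect to the GEE and nothing in the article ranks the two analyses.

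Four stronger readings are tempting but not supported:

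- **That the GEE dilutes the month-6 effect.** The article never says the model has a common arm effect, and step 3 shows that an average can also be larger.
- **That month 12 enters the main GEE.** The article treats it separately.
- **That within-subject tests compete for the primary outcomes.** They are described as additional. Participants are ART-naïve at enrolment, so medication adherence has no baseline value to compare with.
- **That the plan permits success on either test.** No such rule is stated; the 7% to 8% is conditional on one.

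**Conclusion.** The concern holds in this limited form: the article states two between-arm analyses for the month-6 primary outcomes and does not say which is decisive. Under an either-or use, the type I error for each outcome would be about 7% to 8% rather than 5%, assuming a correlation of 0.9 to 0.7 between the tests. How far the two answers could diverge under a real effect depends on assumed effect profiles and on the GEE being read as an average over visits, so those figures illustrate the risk and do not predict it. It should be corrected, and the article describes the trial as ongoing, so this can be done before the outcomes are analysed.

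**What to change.** Name one month-6 between-arm contrast for each primary outcome as the only decisive test, and label the other analysis supportive. Align the abstract's sentence with that choice. Either route works:

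- the month-6 contrast from a GEE or mixed model with visit as a categorical factor and an arm-by-visit term; or
- for adherence, the month-6 two-proportion comparison, which matches the sample-size basis.

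Under either route, adjust the CD4 comparison for baseline CD4 instead of using an unadjusted t-test. The abstract says outcome measures are taken at baseline, so no new data should be needed.

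Two wording changes go with this. Call month 12 a secondary analysis of persistence, as *Primary outcome* describes it, not a sensitivity analysis. Report within-arm changes descriptively and not as evidence of effectiveness, since all participants start ART at enrolment and CD4 can be expected to rise in both arms.

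The cost is wording in the protocol and analysis plan, with the same data and software.

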##### Hospital-visit reminders

A message-reminder module for hospital visits was designed to run autonomously, to facilitate patients’ medication-taking and retention in the ART program. Four follow-up hospital visits are scheduled at months 1, 2, 3 and 6 after ART initiation. Case managers and patients discuss and agree on an exact date for each hospital visit at patients’ convenience. The reminder messages are sent 7 days prior to each scheduled hospital visit. The wording of the reminders is intentionally vague to avoid unwanted disclosure of HIV infection.

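### The complete-data rerun offered to answer GEE's missing-data requirement needs at least as strong an assumption, so it is not a check on it

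*Protocol article*

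**What the plan says.** All the relevant commitments are in the Protocol article, Statistical analysis, Effectiveness of intervention. The analysis is by intention to treat, "using the data collected from all randomized participants in the analysis". For missing outcomes, "Missing endpoints will be imputed by Multiple-Imputation approach". Repeated measures are analysed by GEE, "which allows for the inclusion of all subjects in the analysis regardless of their number of visits"; no weighting for dropout is mentioned. The article then gives a reason and a consequence: "As GEEs require data to be randomly missing, the analysis will be repeated using a subset of participants with complete data". The next sentence adds a further commitment, with no method attached: "A sensitivity analysis will be conducted to determine the impact of dropout and to evaluate additional longer timeframes (month 12").

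Three facts from other sections matter. Sample size estimation allows for 20% attrition at month 6. Data collection has adherence reported by online questionnaire in both arms, with completion prompts and then a phone call for non-responders in either arm. Primary outcome has CD4 measured at physical tests, and hospital visits are the target of an intervention component: "The reminder messages are sent 7 days prior to each scheduled hospital visit".

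**The concern.** The article correctly sees that GEE on available data depends on why data are missing. Its answer is to rerun the analysis in people with nothing missing. That does not relax the assumption; it selects on it more heavily. A statistician who later finds that the two analyses agree may report that the result is robust to dropout, when both could carry the same bias.

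Both co-primary outcomes are open to this. Patients who are missing doses or are unwell may be less likely to answer a questionnaire or attend. For CD4, capture depends on attendance, which the intervention's reminders are meant to improve, so retention could differ by arm as well. The article does not say that dropout will behave like this, but it is the possibility that a check on missing data exists to examine.

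**Working it through.** **Inputs from the article:** 300 per arm; 20% attrition, so 300 × 0.8 = 240 per arm; control adherence 89% at month 6; two-sided alpha 0.05; 80% power. Everything about the dropout mechanism below is assumed.

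**1. The assumptions side by side.**
- Complete case: completeness unrelated to outcome, given arm.
- Unweighted GEE: missingness completely at random, or dependent only on covariates in the model.
- MI under missing at random: missingness may also depend on earlier observed outcomes.

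The rerun is therefore never the most tolerant of the three.

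**2. What drives bias.** In one arm let *m* be the missing fraction, *O* the mean in those observed and *M* the mean in those missing. The true mean is (1 − m)O + mM, so the observed mean is off by O − [(1 − m)O + mM] = m(O − M). The contrast is off by m_I(O − M)_I − m_C(O − M)_C. This holds for adherence and for CD4. If O = M in each arm, the bias is zero however unequal retention is. If *m* and O − M are the same in both arms, the bias cancels.

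**3. One case by hand.** True adherence is 89% in both arms. At month 6, control loses 16% of adherent and 52% of non-adherent participants; the intervention arm loses 20% at random.
- Control retained: 0.89 × 0.84 + 0.11 × 0.48 = 0.7476 + 0.0528 = 0.8004.
- Control observed rate: 0.7476 / 0.8004 = 93.4%.
- Apparent difference: 89.0 − 93.4 = −4.4 points, with 20% lost in each arm as planned.

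**4. All three methods.** A simulation of 2,000,000 participants used 89% adherence in both arms at months 1, 3 and 6 (latent correlation 0.6, assumed). Entries are intervention minus control at month 6 in points; the truth is 0.

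| Assumed dropout | Complete case | GEE | MI (at random) |
|---|---|---|---|
| Completely at random | about 0 | about 0 | about 0 |
| Differs by arm only (73% v 87% retained) | about 0 | about 0 | about 0 |
| In control, on earlier observed adherence | −2.1 | −0.7 | −0.1 |
| In control, on current adherence, every visit | −4.0 | −3.6 | −3.5 |
| In control, on current adherence, month 6 only | −4.5 | −3.9 | −3.9 |

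The last complete-case entry matches the hand calculation within simulation error. In the last two rows the rerun and GEE differ by only about half a point while both are wrong by about 4. In the third row the rerun does separate from the others, but as the worst estimate.

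**5. Scale.** At 240 per arm the standard two-proportion formula gives a detectable increase from 89% of 6.8 points. The article states 9 points; that mismatch is a separate matter and nothing here rests on it. Biases near 4 points are more than half of 6.8.

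**6. Direction.** Informative dropout was placed in the control arm, so these biases run against the intervention. Placing it in the other arm reverses the sign. No CD4 calculation was run.

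**The case against.** The strongest reply is that the rerun is one supplementary line in a plan that already commits to intention to treat, MI and a separate analysis of the impact of dropout. Choosing an imputation model or a not-at-random method is ordinary analysis-plan detail, and that plan is not shown. This stands: the lack of a named not-at-random method is not the finding. What remains is a stated inference that is wrong, and that an analysis plan would carry forward if it followed the article faithfully.

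A second reply is that the rerun has some diagnostic value. That also stands: if dropout follows earlier recorded adherence, it would diverge from GEE and MI. A reader might infer that it can never reveal bias, or that every planned analysis must shift together; the third row of the table contradicts both.

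A reader might also infer that the visit reminders will distort the adherence contrast. One can build such a case. Suppose 20% of each arm are prone to drop out and 50% adherent, the rest 89%; control loses all of them and the intervention arm loses half. The intervention arm then shows (0.8 × 0.89 + 0.1 × 0.5)/0.9 = 84.7% against 89.0%, or −4.3 points, with about 31% rejection under no effect (nearly all favouring control). But this needs hospital-visit reminders to halve questionnaire loss, and the article gives no support for that: questionnaires are online, with prompts and calls in both arms. The reminders bear mainly on CD4. Even there, a retention difference alone causes no bias; dropout must also depend on outcome.

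**Conclusion.** The point holds as a should-fix. The article presents a complete-data rerun as the answer to GEE's missing-data requirement, although that rerun needs an assumption at least as strong as unweighted GEE and stronger than MI under missing at random. Where dropout depends on current unobserved adherence or health, the three can be biased by similar amounts (about 3.5 to 4.5 points in the simulated cases) and their agreement would mislead.

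The logical part does not depend on any figure. The sizes rest on an assumed correlation and assumed dropout rates and are illustrative only. Outcome-dependent dropout is plausible for both co-primaries but is not stated in the article; differential retention is most relevant to CD4. The documents do not support a claim that the trial's result will be biased, or that it will favour the intervention. A more serious rating is not warranted, because MI and a dropout sensitivity analysis are already planned.

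**What to change.** - Remove the sentence's role as the check on the missing-data assumption. Keep the complete-data rerun as descriptive at most.
- Keep the planned MI, imputing separately by arm and using the month 1 and month 3 outcomes that are already collected. This remains a missing-at-random method and is not sufficient alone: in the two-class example above, if adherence at the three visits is independent within class, it moves the spurious difference from −4.3 to about −5.1 points.
- Specify the already planned dropout sensitivity analysis as a delta-adjusted tipping-point analysis of month-6 adherence and month-6 CD4. Shift the imputed values for missing participants by a delta varied separately in each arm, and report the combinations at which the conclusion changes. Keep the month-12 evaluation as a separate item.
- Report retention by arm at each visit, separately for the questionnaire and for CD4.

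The cost is a wording change and modest extra programming, using outcomes already scheduled. It should be settled before outcome data are analysed.
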